Strenuous exercise compared with moderate (Tremblay, et al., 1994; Trapp, et al, 2008) appears to show greater weight loss in some but not all (Jakicic et al. 2003; Tjonna, et al, 2008) studies. Therefore, most people believe that moderate exercise and reduce sedentary activities should be encouraged as a better alternative to increase the daily energy expenditure and to reduce body weight (Westerterp & Plasqui, 2004), mainly because of obese individuals feel more comfort and confidence with the practice of moderate exercise (Piana, et al., 2013). However, few studies have also evaluated the effect of different intensities of exercise on daily energy expenditure in children with overweight.

1. **Objective**

To evaluate the effect of two intensities of exercise on the subsequent spontaneous physical activity energy expenditure among overweight adolescent.

1. **Method**
   1. **Study design**

This is an experimental crossover design, where all selected subjects will undergo three experimental conditions.

All adolescentes enro lled in the 6th and 7th grade in a public school in Niterói, Rio de Janeiro were invited to undergo anthropometric measurements to determine de body mass index (BMI). Only those adolescents classified as overweight according to World Health Organization parameters for age and sex (de Onis, et al., 2007) were included in the study. In order to minimize the risk of stigmatization, eutrophic adolescents will be invite to participate in exercise sessions, with the amount corresponding to 20% of the sample size.

The adolescents will be assessed in five visits. During the first visit, anthropometric measures will be collected. During the second visit, the adolescents will undergo a maximum field test to evaluate aerobic capacity (Leger, et al., 1988). At the end of the test, the maximum heart rate will be determined and the heart rate zone for each experimental session will be calculated. The third and fourth visits will be experimental sessions with different training intensities and the fifth session will be the control session (no exercise), interspersed by a period of one week.(**figure 2**).

[figure not shown]

**Figure 2.** Scheme of the experimental sessions

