The experimental sessions will be structured in two phases: warm-up, training, cool-down. The exercise protocol is different between the experimental sessions (moderate and vigorous) only in the training phase, with similar warm-up and cool-down phases in both sessions. During the warm-up, subjects will be instructed to start walking at a low-intensity, and then increase their pace until they reached values close to 64% of maximum heart rate. In the cool-down phase, adolescents will be instructed to gradually reduce their pace in order to reach heart rate values close to those found at rest. (**figure 3**).

[figure not shown]

**Figure 3.** Warm-up and cool-down characteristics

The main part of the moderate session (MS) consist of 4 sets of 10 minutes walking at moderate intensity (64% to 76% of maximum heart rate), interspersed with 5 minutes of light walking (below 64% of maximum heart rate) for recovery between sets. (**figure 4**).

[figure not shown]

**Figure 4.** Main part of the moderate session

The main part of vigorous session (VS) consist on 4 sets of 10 minutes running at vigorous intensity (77% to 95% of maximum heart rate), interspersed with 5 minutes of light walking (below 64% of maximum heart rate) for the recovery between sets. (**figure 5**).

[figure not shown]

**Figure 5.** Main part of the vigorous session

During the two experimental sessions, the adolescents will be supervised by a trained exercise physiologist to ensure that they will perform the intervention protocol properly. The target heart rate will be monitored using heart rate monitors. One week was defined as a washout period (**figure 2**).

During the exercise sessions and for a period of six days, energy expenditure and the amount of physical activity will be evaluated through accelerometers. It consists of a small device that is placed at the hip region and should be removed only during bathing or during the practice of aquatic activities. The use of this device is considered safe, however, for an extended period, may cause discomfort. The adolescents will be informed not to perform physical exercises in the three days before each session, and not drinking alcohol, coffee or any other stimulant in the 24 hours prior to each session.

- 1. **Sample size**

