Sample size was calculated based on a mean difference in daily energy expenditure between sessions of 110 kcal (Wang, et al., 2006) with a coefficient of variation equal to 1 (standard deviation of 110 kcal) (van Belle, 2008). The sample size required for the study, with an α of 0.05 and β of 0.10 and estimating a refusal rate of 20%, was 27 children (Julious, 2009).

- 1. **Measurement procedures**
     1. **Anthropometric measurements**

Body weight will be measured using a portable electronic scale (Tanita BC -558 Japan) with a capacity of 150 kg and precision of 50g, while wearing light clothes and no shoes. Height will be measured using a portable stadiometer (Alturexata, Brazil) with an amplitude of 200 cm and variation of 0.1 cm. Participants will be instructed to remain without shoes, feet together and keeping the head in the Frankfurt plane (Madsen, et al., 2008). Two measurements will be made and considered the mean values ​​for analysis. The classification of nutritional status will be based on BMI (kg/m2) cutoff points recommended by the World Health Organization (de Onis, et al., 2007).

- - 1. **Shuttle run test**

Cardiorespiratory fitness will be assessed by a maximum field test, specific to the age of the study group. The shuttle run, is a valid test (Leger et al., 1988) and widely used in studies with adolescents worldwide (Jimenez-Pavon et al ., 2013; veses, et al, 2014). The purpose of this test is to estimate the maximum oxygen consumption. It is a progressive, maximum and indirect test. Participants are placed at the starting line and begin the test with the first beep. They must arrive at the marked location, bypassing the line, before sounding the next beep. The direction changes must be made to stop and start the other way, avoiding curvilinear paths. Every minute, the time between beeps will decrease, which mean an increase in the speed. The test will be completed with the participant's withdrawal, or when it fails to reach the scored line two consecutive times. A doctor will be present during the test for possible complications. Each participant will use a heart rate monitor during the test and the maximum heart rate will be recorded. Thus, the intensity of each exercise session (moderate and vigorous) will be calculated, individually, according to the percentage of the maximum frequency established for moderate and vigorous intensity (Physical Activity Guidelines Advisory Committee, 2008).

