- - 1. **Energy expenditure measurements**

The physical activity energy expenditure during one week will be assessed through Actigraph accelerometers, wGT3X-BT model. It is a portable, lightweight and non-invasive device, providing an objective measurement of physical activity. The accelerometer will be placed on the day before each experimental session, at the same time and removed after one week.

This device is often used in epidemiological studies to evaluate the recommendations of physical activity for children and adolescents, as well as providing an estimate of energy expenditure derived from the activities. In order to proceed with the evaluations, threshold values ​​were developed to fractionate the intensity into categories: sedentary, light, moderate and intense.

The border points that will be used for each intensity range have been proposed by Evenson (2008), which below 100 counts per minute, physical activity is classified as sedentary between, 100 and 2296 counts per minute as light activity, between 2296 and 4012 as moderate and above 4012 vigorous physical activity. These points have shown greater precision to classify physical activity intensity than other points established in other studies (Trost, et al., 2011).

The sampling period (epoch) in this study is 5 seconds to capture the possibility of minor variations in movements performed by adolescents (Trost, et al., 2005). Days with less than 600 minutes of recorded data or more than 60 minutes counts of consecutive zeros, will be excluded from the analysis (Choi et al., 2011).

Adolescents will be instructed not to take out the device during that time, except for the period of the bath and while practicing water activities.

- 1. **Data analysis**

The descriptive analyses will calculate the mean and standard deviations for continuous and percentages for categorical variables. Differences in daily and accumulated energy expenditure between exercise sessions will be performed using linear mixed models, which takes into account the correlations between repeated measures over time.

The analysis will be performed in SAS 9.3 software (Statistical Analysis System, USA) and statistical significance set at p<0.05 for all analyses.

•

•

•

•

1. **References**

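### No random or balanced order is stated for the moderate and vigorous sessions, and the control always comes last, so session effects can be confounded with study week

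*Protocol*

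**What the plan says.** The Objective section sets the question: "To evaluate the effect of two intensities of exercise on the subsequent spontaneous physical activity energy expenditure among overweight adolescent". Under Method, the Study design section states: "This is an experimental crossover design, where all selected subjects will undergo three experimental conditions". The five visits are then laid out. Anthropometry is at visit 1 and the maximal shuttle run at visit 2. For the sessions themselves, "The third and fourth visits will be experimental sessions with different training intensities". Visit 5 is reserved for the condition without exercise; of this the text says: "the fifth session will be the control session (no exercise), interspersed by a period of one week". The same section adds: "One week was defined as a washout period".

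The control therefore has a fixed position, while the two intensities share visits 3 and 4 without either being assigned to a visit. The readable text does not mention random, balanced or counterbalanced order for this trial. Randomisation is mentioned only for studies cited in the Background.

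The Data analysis section says "Differences in daily and accumulated energy expenditure between exercise sessions will be performed using linear mixed models", a method "which takes into account the correlations between repeated measures over time". The Sample size section says "Sample size was calculated based on a mean difference in daily energy expenditure between sessions of 110 kcal", with an SD of 110 kcal, α 0.05, β 0.10, a 20% refusal rate and 27 children.

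**The concern.** A crossover separates condition from time only if different participants meet the conditions in different orders. Without that, a change in activity from one week to the next cannot be told apart from an effect of the session.

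The weeks differ on the Protocol's own account. The week of visit 3 follows the maximal shuttle run visit and, as far as the text shows, is the first in which the accelerometer is worn. The week of visit 4 follows a supervised exercise session and a week of wearing the device, which the Study design section says may become uncomfortable. Weather and the school calendar may also change.

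The direction of the error depends on the order. If moderate came first for everyone, a fall in activity would look like compensation after vigorous exercise, which the Background reports for some studies, and a rise would hide it. If vigorous came first, the reverse would hold. For the control the problem does not depend on that order, because every adolescent meets it in week 3.

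**Working it through.** **Inputs.** From the Sample size section: difference 110 kcal/day, SD 110 kcal, α 0.05, power 0.90, refusal 20%, N = 27. From the Study design section: three conditions, two exercise sessions at visits 3 and 4, control at visit 5. Assumptions: a two-sided test, and the size of any week shift, for which the Protocol gives no figure.

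**1. Which SD does the plan use?** The text does not say whether 110 kcal is a within-person SD or the SD of a paired difference.

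- Within-person SD: n = 2 x (1.960 + 1.282)² x (110/110)² = 21.0, rounded up to 22. Then 22 x 1.2 = 26.4, rounded up to 27, the stated figure. (Dividing by 0.8 gives 27.5, or 28.)
- SD of the paired difference: n = (1.960 + 1.282)² = 10.5, rounded up to 11. Then 11 x 1.2 = 13.2, or 14, about half the stated figure.

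The within-person reading fits the plan and is used below.

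**2. Can the contrasts be estimated once week is in the model?** The rank of the design matrix with adolescent, condition and week effects shows:

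| Order of conditions | Moderate vs vigorous | Moderate vs control |
|---|---|---|
| One order for all, control last | not estimable | not estimable |
| Exercise order varies, control last | estimable | not estimable |
| All six orders of the three conditions | estimable | estimable |

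The same applies to vigorous versus control. Modelling the correlation between repeated measures does not change this, because a week shift acts on the mean.

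**3. Bias in vigorous versus moderate without a week term.** Let q be the share of adolescents with one order. Then bias = shift x (2q − 1):

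- q = 1 passes the whole shift.
- q = 0.75 passes half.
- q = 0.5 passes none.

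**4. False-positive rate under a common order (q = 1).** About 22 adolescents are evaluable (27 x 0.8 = 21.6). SE = √2 x 110/√22 = 33.2 kcal. With no true difference, the paired t-test (21 df, two-sided 5%) rejects with the noncentral-t probability at noncentrality shift/33.2:

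| Assumed shift (kcal/day) | Share of 110 kcal | Noncentrality | Rejection rate |
|---|---|---|---|
| 0 | 0% | 0 | 5.0% |
| 11 | 10% | 0.33 | 6.2% |
| 22 | 20% | 0.66 | 9.7% |
| 33 | 30% | 0.99 | 15.8% |
| 55 | 50% | 1.66 | 35.3% |

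A shift can also hide an effect. A true 110 kcal difference opposed by a 55 kcal shift leaves 55 kcal to detect, and power falls from 88.5% to 35.3%.

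**5. Price of the remedy.** Power for 110 kcal is 88.5% with one order (21 df) and 88.4% with two balanced orders and a week term (20 df).

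**The case against.** The strongest reply is that the text assigns neither intensity to a visit. The wording fits an order that varies between adolescents as well as a common one, and under an even split the bias in moderate versus vigorous is zero. Figure 2 is cited for the session scheme and the washout, and it may show the order. This stands. The harm to that contrast is therefore conditional, and the point is limited to the readable text.

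Three stronger readings are tempting, and the Protocol does not support them:

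- *Moderate always came first.* The text describes moderate before vigorous, but order of description is not order of conduct.
- *Staff choose the order.* Nothing in the text suggests it.
- *The missing week term is itself a fault.* Period and sequence terms are commonly left to an SAP, and under one common order a week term could not rescue the contrast.

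It is also fair to object that reading 110 kcal as the SD of the difference would give larger rates (61% at a 55 kcal shift), but that reading does not reproduce N = 27.

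None of this answers the control. Its place at visit 5 is stated outright, and varying visits 3 and 4 alone would not cure it. Nor can an SAP supply the order, because it is set when visit 3 takes place.

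**Conclusion.** The point holds in conditional form for the two intensities and without condition for the control. The readable Protocol states no random or balanced order for the exercise sessions. If one order is used for all, intensity is fully confounded with week. If the split is uneven and week is not modelled, part of any shift passes through. Exercise versus control is aliased with week 3 whatever happens at visits 3 and 4.

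A reader might infer that the moderate-versus-vigorous result is bound to absorb any week change. That would need a common order, which the text does not state.

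The false-positive rates of about 6%, 10%, 16% and 35% rest on a common order, 22 evaluable adolescents, a two-sided paired test, 110 kcal as the within-person SD, and assumed shifts of 11, 22, 33 and 55 kcal/day. They show sensitivity and do not predict the drift. The point still warrants a change to the Protocol, because a missing balance of order cannot be restored after the sessions are run.

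**What to change.** In the Study design section, state that each adolescent is allocated at random to one of the six orders of moderate, vigorous and control, in balanced numbers. Use a computer-generated list made before visit 3 and concealed from those who run the sessions. At the least, allocate half to moderate-first and half to vigorous-first. This protects the contrast between intensities but leaves the control confounded with week 3, and the Protocol should then say so. If Figure 2 already shows a random order, write it into the text.

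In the Data analysis section, include study week (period) as a fixed effect in the mixed model and report the contrasts from that model.

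The cost is a short amendment and one list, with no more participants, visits or measurements. Different session types must run in the same week, and a few degrees of freedom are lost (two for a three-level week effect). With 27 adolescents the six orders cannot be exactly equal, so each would hold four or five.

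### The no-exercise control is fixed at the last visit, so the exercise-versus-control contrasts cannot be separated from study week

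*Protocol*

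**What the plan says.** The Study design section sets out the general scheme: "This is an experimental crossover design, where all selected subjects will undergo three experimental conditions". It then assigns conditions to visits: "The third and fourth visits will be experimental sessions with different training intensities and the fifth session will be the control session (no exercise". Successive sessions are a week apart, and the same section adds that "One week was defined as a washout period". Nothing in the protocol lets control come earlier. Figure 2, cited for the scheme, is not available here, but the sentence that cites it already puts control at the fifth visit.

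The Objective is "To evaluate the effect of two intensities of exercise on the subsequent spontaneous physical activity energy expenditure among overweight adolescent". On measurement, the Energy expenditure section says: "The accelerometer will be placed on the day before each experimental session, at the same time and removed after one week". The Data analysis section says: "Differences in daily and accumulated energy expenditure between exercise sessions will be performed using linear mixed models", with allowance for correlation between repeated measures.

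The Sample size section uses a difference of 110 kcal/day between sessions and an SD of 110 kcal, with alpha 0.05, beta 0.10 and 20% refusal, and arrives at 27 children.

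**The concern.** A crossover protects its comparisons from time trends by letting each condition occur in different periods. Here one of the three conditions never moves. Anything that makes the third study week differ from the first two is read as a difference between exercise and no exercise. Examples are getting used to a hip-worn device, weather, the school calendar, or something left over from the two exercise weeks. The washout week is aimed at carry-over only; it does nothing about a trend over weeks.

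The background sections are built around compensation: whether adolescents move less after exercise than they otherwise would have. The no-exercise week is the only planned reference for that question, and it is the one condition tied to a fixed study week. A shift could go either way, so it could create apparent compensation or hide real compensation.

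**Working it through.** **1. The plan's own sample size.** Inputs from the Sample size section: difference 110 kcal, SD 110 kcal, alpha 0.05 (taken as two-sided), power 0.90, refusal 20%. Reading 110 kcal as the within-subject SD:

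n = 2 × (1.960 + 1.282)² × 110²/110² = 2 × 10.507 = 21.01; 21.01/0.8 = 26.3, so 27.

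The stated 27 reproduces, and the sample size is not at fault. On this reading the SD of a paired difference is 110 × √2 = 156 kcal, and about 22 adolescents are evaluable (21.01 rounded up; also 27 × 0.8 = 21.6). If 110 kcal were instead the SD of the differences, the same formula would give 11, or 14 after refusals, which does not match 27. That value is kept below only as a sensitivity case.

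**2. Can the contrasts be estimated?** The model has subject, week (three levels) and condition. M is moderate, V vigorous, C control, with one subject per listed order. A contrast is estimable if it lies in the row space of the design matrix.

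| Orders used | Rank / columns | M−C and V−C | M−V |
|---|---|---|---|
| M-V-C only | 3 / 5 | no | no |
| M-V-C and V-M-C | 5 / 6 | no | yes |
| Three-sequence Latin square | 7 / 7 | yes | yes |
| All six orders | 10 / 10 | yes | yes |

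In the first two rows control coincides with week 3. Adding subjects repeats the same rows and does not raise the rank relative to the columns needed.

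**3. What if week is restricted to a straight line?** With M-V-C and V-M-C both used, a linear week term makes M−C and V−C estimable. The variance per subject rises from 2σ² to 6.5σ², a factor of 3.25. With the single order M-V-C, even a linear term leaves them inestimable.

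**4. Size.** The documents give no week effect, so the shift δ between control's week and the exercise weeks is assumed. With no true exercise effect, a two-sided paired t-test rejects with probability P(|T| > 2.080), where T is noncentral t with 21 degrees of freedom and λ = δ√22/SD. For δ = 30 and SD = 155.6, λ = 30 × 4.690/155.6 = 0.90 and the rejection rate is 0.139.

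| Shift, kcal/day | Share of 110 kcal | SD of differences 156 | SD of differences 110 |
|---|---|---|---|
| 0 | 0% | 5% | 5% |
| 10 | 9% | 6% | 7% |
| 30 | 27% | 14% | 23% |
| 45 | 41% | 25% | 45% |
| 60 | 55% | 41% | 68% |

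A steady drift of 30 kcal/day per week, for example, gives a bias of 30 against whichever condition is always in week 2 and 60 against whichever is always in week 1. If moderate and vigorous are balanced over visits 3 and 4, each contrast carries (30 + 60)/2 = 45.

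**The case against.** Four points can fairly be made for the plan.

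- **The intensity comparison survives.** The Objective names two intensities, and the analysis sentence speaks of exercise sessions. A reader might infer that the whole crossover is invalid. The documents do not support that: moderate versus vigorous does not depend on where control sits. It does need the order at visits 3 and 4 to vary. The text does not state that order, and the figure that may show it is missing, so it cannot be said that the order is fixed.
- **Some repair is conceivable.** A reader might also infer that no later analysis could help. That is too strong. The device is fitted the day before each session, so every week has a pre-session day, and change from that day would remove an additive week shift. A linear drift could be modelled if the order at visits 3 and 4 varies. Neither approach is planned. The first rests on a single day that falls within the three days in which exercise is to be avoided, and both need assumptions that these data cannot test.
- **The drift may be small.** At 10 kcal/day the error rate barely moves. This stands, and it is why a range is shown; none of the rates is a prediction.
- **Model terms may be in an analysis plan that is not shown.** This is accepted, and their absence is not the point. The order of visits is a design rule stated in the protocol, and adding a week term does not make the contrasts estimable while control stays last.

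**Conclusion.** The point holds for moderate versus control and vigorous versus control. As written, these are before-after comparisons within a study called a crossover. With unrestricted week effects they are not estimable, and without a week term any week-3 shift passes into them in full. This follows from the text alone and needs no assumption about drift.

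The consequence in error rates does need assumptions: the size of the shift, 22 evaluable adolescents, and a paired-difference SD of 156 kcal (110 as the alternative). Over shifts of 10 to 60 kcal/day the false-positive rate runs from about 6% to 41%, or 7% to 68%, against a nominal 5%.

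Because compensation is the question that motivates the study and the correction is cheap, this should be settled before sessions begin.

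**What to change.** Randomise each adolescent to an order of all three conditions, so that control can fall at visit 3, 4 or 5, and include week in the mixed model. A three-sequence Latin square or all six orders (four to five adolescents per order with 27) makes every contrast estimable. Under either, adjusting for week leaves the contrast variance at 2σ² per subject. All six orders have the further merit that each condition follows each other condition equally often; in a single three-sequence square each condition always follows the same one, so carry-over is less well spread.

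The cost is a short amendment, an allocation list and one model term. The sample size and number of visits do not change. The drawback is practical: adolescents in different conditions must be handled on the same session day.

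If control must stay last, the protocol should describe exercise versus control as a non-randomised comparison confounded with time. It should then limit randomised inference to moderate versus vigorous, with the order at visits 3 and 4 randomised.

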In another study, Duncan et al., (2005) compared the effects of the hike in different intensities and weekly frequency in cardiorespiratory fitness and lipid profiles in 492 healthy adults. The experimental protocol contemplated four different conditions: moderate / low frequency, moderate intensity / high frequency, high intensity / low frequency and high intensity / high frequency. The training area was determined at 45% to 55% and 65% to 75% of the heart rate reserve for moderate and strong intensities, respectively. Participants in the low frequency weekly group were instructed to walk 3 to 4 times a week while the high-frequency group of 5 to 7 days per week. After 24 months, none of the groups showed statistically significant change in body weight. Also, Tjonna et al., (2008) examined the effects of exercise training versus intense in variables associated with cardiovascular function in 32 patients with metabolic syndrome and concluded that the two exercise programs were equally effective in reducing blood pressure, weight and body fat.

Wang et al. (2011) randomized 36 obese postmenopausal women in two groups. The first group was asked to perform treadmill walking at a moderate intensity (45% - 50% of maximal oxygen consumption) while the second group at a vigorous intensity (70% - 75% of maximum oxygen consumption). After five months energy expenditure among the women in the group who performed moderate activity was higher on days when they performed the exercise (577.7 ± 219.7 kcal.d-1) compared to the days when not performed ( 450.7 ± 140.5 kcal.d-1), however, the overall difference was much lower than the one spent on the sessions (127.0 ± 188.1 kcal.d-1). In women who performed vigorous exercise, energy expenditure on days with exercise (450.6 ± 153.6 kcal.d-1) was lower compared to days without exercise (519.2 ± 127.4 kcal.d-1) . The authors conclude that there is a compensatory effect caused by exercise that occurs primarily with high-intensity activities.

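### The sample-size SD is set equal to the difference to be detected, so 27 follows for any effect size and no variability figure in the protocol supports the 90% power for 110 kcal

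*Protocol*

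**What the plan says.** The Sample size section of the protocol (under Method) takes a "mean difference in daily energy expenditure between sessions of 110 kcal" from a cited study. It sets the variability "with a coefficient of variation equal to 1 (standard deviation of 110 kcal"), citing a textbook, and states that the number required, "with an α of 0.05 and β of 0.10 and estimating a refusal rate of 20%, was 27 children". It does not say whether the 110 kcal SD belongs to one period's value or to the difference between two sessions in the same adolescent.

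The Study design section matters here: "This is an experimental crossover design, where all selected subjects will undergo three experimental conditions". Comparisons between sessions are therefore within person.

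The only SD of a within-person difference in the protocol is in the Background, under the effects of exercise on energy expenditure. For the moderate-intensity group of a cited trial that "randomized 36 obese postmenopausal women in two groups", it reports that "the overall difference was much lower than the one spent on the sessions (127.0 ± 188.1 kcal.d-1"). The same paragraph gives the mean and SD of daily expenditure on exercise and non-exercise days in both groups.

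**The concern.** A coefficient of variation relates an SD to the mean of the outcome. Here it multiplies the difference to be detected. That fixes the ratio of effect to SD at 1, so the 110 kcal cancels and the sample size carries no information about how large a difference the trial can detect.

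The objective is to learn whether exercise at two intensities changes later spontaneous activity expenditure, and a null result is one of the informative outcomes. Such a result would be read against 90% power for 110 kcal. If the variability behind that figure was not estimated from anything, the reader cannot tell how strong a null finding is.

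**Working it through.** **Inputs.** Sample size section: difference 110, SD 110, α 0.05 (taken as two-sided), β 0.10, 20% refusal. Background: moderate group 577.7 ± 219.7 and 450.7 ± 140.5, difference 127.0 ± 188.1; vigorous group 450.6 ± 153.6 and 519.2 ± 127.4, with no SD of the difference given.

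**1. Reproducing 27.** (1.960 + 1.2816)² = 10.507. With 110 as a within-period SD, the SD of the difference is √2 × 110 = 155.6, and n = 2 × 10.507 × (110/110)² = 21.01. Then 21.01 / 0.8 = 26.3, rounded up to 27. One-sided α gives 18 evaluable and 21 to 23 enrolled, so the calculation was two-sided.

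**2. The effect cancels.** With SD = difference, the last factor is always 1. Differences of 20, 50, 110 and 500 kcal each give 21.01, and so 27.

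**3. The other reading.** With 110 as the SD of the within-adolescent difference, n = 10.507 × (110/110)² = 10.5, or 13 by paired t. 13 / 0.8 = 16.25, so 17 enrolled. This does not give 27. With 22 evaluable, power would be above 99%.

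**4. Is a coefficient of variation of 1 plausible for the outcome?** The four daily values in the Background give 219.7/577.7 = 0.38, 140.5/450.7 = 0.31, 153.6/450.6 = 0.34 and 127.4/519.2 = 0.25. None is near 1.

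**5. What 188.1 is.** 577.7 − 450.7 = 127.0, so 188.1 is the SD of the paired difference. The implied correlation between the two kinds of day is (219.7² + 140.5² − 188.1²) / (2 × 219.7 × 140.5) = 32,626.7 / 61,735.7 = 0.53.

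**6. The vigorous group, under an assumption.** If its correlation is also 0.53, the SD of its difference is √(153.6² + 127.4² − 2 × 0.53 × 153.6 × 127.4) ≈ 138 (using the unrounded correlation).

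**7. Power for 110 kcal** (paired t, two-sided 0.05). 27 less 20% is 21.6, taken as 22.

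| SD of difference | 22 evaluable | all 27 analysed |
|---|---|---|
| 138 (assumed, step 6) | 94.5% | 98% |
| 156 (reading that gives 27) | 88.5% | 94% |
| 188.1 (moderate group) | 74% | 83% |

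The normal approximation at 22 gives 91.3% for 156 and 78.3% for 188.1. At 188.1, 90% power is reached at about 136 kcal with 22 and about 122 kcal with 27. For 110 kcal it would need 33 evaluable.

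**The case against.** The strongest defence is that nothing is miscalculated. The usual crossover formula with 110 as the within-subject SD gives 27, and on those inputs power at 22 evaluable is 91.3% by the normal approximation or 88.5% by paired t, close to what is stated. The protocol also fixes the effect at 110 kcal from a cited source, and cites others for the coefficient of variation and the method. Those sources may contain support that cannot be checked here. All of this stands, and it limits the point to an unsupported and unnamed input. It does not answer the point, because the section shows no variability figure and the SD moves with whatever difference is chosen.

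A reader might infer from the 188.1 kcal figure that the trial really has 74% power, or misses a true 110 kcal difference one time in four. The documents do not support that. The figure compares exercise with non-exercise days in one group of obese postmenopausal women after five months of training, whereas this trial studies overweight adolescents after single sessions. The vigorous group of the same study, under the assumed correlation, gives power above 90%. In addition, the protocol speaks of refusal, which need not mean loss after enrolment, and it plans a mixed model on repeated daily values, which a paired t-test on one value per period represents only roughly.

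For the same reasons the documents do not show that 27 is too few.

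**Conclusion.** The point holds as a fault in the basis of the sample size, not in its arithmetic. The SD is derived from the effect, its type is not stated, and the two possible readings lead to 17 or 27 enrolled. The 90% power for 110 kcal therefore rests on no variability figure in the protocol. Across the SDs of the difference that can be drawn from the document (138 assumed, 156, 188.1), power for 110 kcal runs from 74% to 94.5% with 22 evaluable, and from 83% to 98% with all 27.

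These figures assume two-sided 0.05, a paired t-test on one value per period, and for 138 an equal correlation in the two groups of the cited study. The 74% is the pessimistic end of a sensitivity range.

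**What to change.** Rewrite the sample-size paragraph as follows.

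- Drop the coefficient of variation. State that 110 kcal is the within-period SD, corresponding to an SD of the within-adolescent difference of about 156 kcal, and give the empirical source for it.
- State that α is two-sided, and that 27 enrolled less 20% leaves about 22 evaluable.
- Replace the single 90% figure with the range for 110 kcal: about 94.5%, 88.5% and 74% with 22 evaluable, and about 98%, 94% and 83% with 27, at SDs of the difference of 138, 156 and 188.1.
- Add that at 188.1 the difference detectable with 90% power is about 136 kcal (22) or 122 kcal (27).
- Say plainly that 188.1 comes from the moderate-intensity group of a study of obese postmenopausal women, that 138 rests on an assumed correlation, and that neither is an estimate for overweight adolescents.

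Enrolment and procedures stay as they are. The cost is one rewritten paragraph and a less favourable statement of power.
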